
 National Agency for the Control of AIDS. Modes of HIV transmission in Nigeria: analysis of the distribution of new infections in Nigeria and recommendations for prevention. 2010.

Nigeria, about 7.7% to 78.7% of HIV positive pregnant women who access antenatal care have HIV negative male sex partners. The highest rates occurred among married couples in Southern Nigeria. Among the sero-discordant couples enrolled in the FHI 360 program, women were 11 times more likely to be the HIV positive partner than the HIV negative partner.

Also, preliminary data from the IHVN project in Jos, Nigeria identified discordant couples as having elevated risk of acquiring HIV infection due to low condom use (<30%) between partners, the majority (>84%) of whom are married. IHVN records show 13% HIV seroprevalence in females and 7% in males in this group, much higher than the national average of 3.4%. Discordant couples make up about 3% of the total number of HIV positives in the IHV-N PEPFAR network.

Understanding HIV-1 prevention choices and targeting prevention strategies to this group are public health priorities. In particular, HIV-1 serodiscordant couples have been specifically identified as a priority population for implementation of antiretroviral-based HIV-1 prevention, given their high risk, smaller number for targeting relative to the general population, ability to be targeted for prevention efforts through promotion of couples HIV-1 counseling and testing, and the clear advantage to the partnership in avoiding HIV-1 transmission. Importantly, both ART (HPTN 052) and PrEP (Partners PrEP Study) have demonstrated high efficacy for HIV-1 protection when used by members of HIV-1 serodiscordant couples. WHO is poised to release guidelines for counseling and prevention for HIV-1 serodiscordant couples, which will include ART and PrEP as potential prevention strategies.

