**3.2 Secondary objectives**

- 3.2.1 Assess client, facility and community level factors influencing demand, preferences, uptake and adherence for antiretroviral-based HIV-1 prevention in Nigeria
- 3.2.2 Assess user preferences among high-risk HIV-1 serodiscordant couples for ART initiation for HIV-1 infected partners and PrEP for HIV-1 uninfected partners.
- 3.2.3 Ascertain initiation of and adherence to PrEP among HIV-1 uninfected partners as a bridge to ART.
- 3.2.4 Look for evidence of risk compensation by HIV-1 serodiscordant couples on PrEP or TasP, migration from condom use.
- 3.2.5 Determine the ART resistance profile developed by HIV-1 serodiscordant couples on PrEP during the study; assess that profile's prevalence.
- 3.2.6 Model the resources needed to provide PrEP and TasP for other specific target groups who are also at high risk of contracting HIV.

**Objective 3.2.1: Assess client, facility and community level factors influencing preferences, uptake and adherence for antiretroviral-based HIV-1 prevention in Nigeria**

Understanding factors that influence couples' preferences and their likelihood to initiate and adhere to PrEP and/or ART in a real-world setting is critical for providers who will counsel HIV-1 serodiscordant couples.

Using interviewer-administered questionnaires, assessments will be made of the correlates to preferences, uptake and adherence to ART and PrEP. These will include characteristics of sexual risk (e.g., sexual frequency, condom use, whether the HIV-1 uninfected partner reports outside partners); depression and substance use; gender of the HIV-1 uninfected partner; fertility intentions; partnership characteristics (whether the couple is cohabiting at baseline, has children, is together throughout follow-up, whether members have other partners, and whether the HIV-1 infected partner initiates ART), and clinical characteristics of the HIV-1 infected partner (e.g., CD4 count, WHO stage).

Facility level factors would be assessed. This would include the impact of training on quality of service delivery and perceived changes by clients at the service sites, effective communication strategies, adherence counselling, use of centralized vs decentralized services for drug access, time spent and costs for travels to facility. The study shall also assess the impact of use of home self-test kits (OralQuick®) for partner recruitment and uptake of PrEP and TasP by serodiscordant couples. See the attached Protocol B.

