**Objective 3.2.4: Look for evidence of risk compensation by HIV-1 serodiscordant couples on PrEP or TasP.**

Risk compensation when using PrEP occurs when patients, perceiving PrEP to reduce their risk of HIV acquisition, start to engage in riskier behaviors or to reduce their use

of other protection methods such as condoms. Clinical trials on PrEP have not found significant evidence of risk compensation, but the possibility cannot be ruled out in real-world practice.

*The primary measure of this objective is reduction in rate of use of condom per couple on PrEP; and rate of increase in STI diagnosed per couple on PrEP. This data will be generated from the clinical data and the behaviour surveillance data.*

**Objective 3.2.5: Measure the probability of participants developing a resistance to Truvada during the course of the study.**

PrEP and TasP studies have tried to address the issue of drug resistance to tenofovir and emtricitabine. Studies in HIV-1-infected individuals followed small numbers of patients for a short time. Very few cases of resistance have been reported, but participants in these clinical trials are monitored under rigorous clinical trial conditions that do not replicate real world events. Studies in macaques were well designed, but used SHIV, which has an attenuated course of infection. The available information suggests that the probability of emergence of drug resistance is small. Infections that occurred despite use of PrEP had reduced peak viremia, which could reduce HIV transmissibility. Mathematical modeling suggests that, although transmitted drug resistance may under some circumstances increase, the benefits of PrEP outweigh the risks associated with resistance. Tenofovir and emtricitabine are, however, recommended in first-line treatment drugs in Nigeria. It is therefore important to confirm the expected low incidence of drug resistance in daily practice. This demonstration project will conduct a surveillance of drug resistance to Truvada in patients who take PrEP.

*The primary measure of this objective is an estimate of the prevalence of ART resistance that developed in patients who seroconverted while using PrEP.*

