At enrollment HIV-1 uninfected women will have a pregnancy test to confirm eligibility (must not be pregnant to complete enrollment). Women will be asked about pregnancy at every scheduled follow-up visit and pregnancy testing will be done when clinically indicated (e.g., missed menses, participant request); PrEP will be continued during pregnancy and breastfeeding. In addition, pregnant women will be advised to continue with their follow up visits. When these participants no longer have a positive pregnancy test, the pregnancy outcome will be documented.

Every 6 months, in addition to regular quarterly visit procedures, CD4 counts and plasma viral loads will be done for HIV-1 infected partners.

Clinical safety will be assessed pre-, during- and post-enrollment. Laboratory safety assessments will be done at enrollment, month 12, study exit and additionally if indicated. At these visits, blood samples will be collected for urea, electrolytes, creatinine, liver function tests, full blood count, calcium and phosphate levels.

All HIV-1 infected partners who are interested in starting ART independent of their becoming eligible for ART under the current national guidelines, will be offered ART. Once the HIV-1 infected partner has been using ART for 6 months, PrEP will be discontinued for the HIV-1 uninfected partner, after counseling to the couple.

During follow-up, HIV-1 infected and uninfected participants will complete a quantitative interview to capture evolution in preferences to uptake of antiretroviral-based HIV-1 prevention and fertility intentions and any risk compensation behaviours. Questionnaires will be administered separately to both members of couples.

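### The named measure for Objective 3.2.4 is narrower than the protocol's own definition of risk compensation and could miss more condomless sex or a new outside partner

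*Protocol*

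**What the plan says.** Objective 3.2.4 explains that risk compensation occurs when people who feel protected by PrEP "start to engage in riskier behaviors or to reduce their use" of other protection such as condoms. That description has two limbs: riskier behaviour, or less protection.

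The primary measure named under the same objective has two items: the "reduction in rate of use of condom per couple on PrEP" and the "rate of increase in STI diagnosed per couple on PrEP". On sources it adds: "This data will be generated from the clinical data and the behaviour surveillance data".

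Related information appears elsewhere in the protocol, for other purposes:
- Objective 3.2.1 collects "characteristics of sexual risk (e.g., sexual frequency, condom use, whether the HIV-1 uninfected partner reports outside partners" as correlates of preference, uptake and adherence.
- Section 11.5 has follow-up interviews, held separately with each partner, that cover preferences "and fertility intentions and any risk compensation behaviours".
- Section 13.1 lists coital acts and condom use among the variables whose effect on uptake and seroconversion will be assessed.
- Section 14.3 has the Protocol Team watch trends in risk behaviour.

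Sections 6.0 and 11.5 make STI diagnosis and management syndromic.

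**The concern.** Only the second limb of the description has a behavioural measure. A condom rate does not say how many acts take place or with whom. A couple having more sex at the same condom rate, or an uninfected partner who acquires an outside partner, fits the first limb but does not move the condom item.

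Objective 3.2.4 itself says risk compensation cannot be excluded in ordinary practice, and section 1.5 gives understanding sexual behaviour outside trials as one reason for demonstration projects. The results are meant to feed a national scale-up plan. A flat condom rate could be carried into that plan as reassurance about sexual behaviour in general, which it cannot give.

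**Working it through.** The protocol gives no figure, baseline or power calculation for this objective, so there is nothing of its own to reproduce. The check is whether the named items respond to the behaviours that the description covers.

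**Step 1. Condom rate and act frequency.** Condomless acts = acts × (1 − condom rate). The act counts and the 30% rate are assumptions for illustration.

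| Scenario | Condomless acts before | Condomless acts after | Change | Condom rate |
|---|---|---|---|---|
| 8 to 12 acts per month at 30% | 8 × 0.70 = 5.6 | 12 × 0.70 = 8.4 | +50% | 0 points |
| 6 to 12 acts per 3 months at 30% | 6 × 0.70 = 4.2 | 12 × 0.70 = 8.4 | +100% | 0 points |
| 8 to 10 acts per month, 30% falling to 24% | 8 × 0.70 = 5.6 | 10 × 0.76 = 7.6 | +36% | −6 points |

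The first two rows are invisible to a rate read as a share of acts, and this holds for any act counts. In the third row the rate moves in the right direction, so the change is detected in kind but its size is not conveyed.

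**Step 2. Does another reading of the rate help?** The protocol does not define it.
- Read as protected acts per month, the first scenario goes from 8 × 0.30 = 2.4 to 12 × 0.30 = 3.6. That is a rise, so no reduction is shown.
- Read as the share of couples using condoms, it stays the same if nobody stops.

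**Step 3. Outside partners.** Neither named item records whether the uninfected partner has one. An outside partner can reach the measure only indirectly, through a diagnosed STI.

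**Step 4. Do STI diagnoses close the gap?** Only partly.
- Syndromic diagnosis does not pick up infection without symptoms.
- More condomless sex within a couple in which neither partner carries an STI produces no diagnosis.
- Section 14.4.1 cites a result from the TDF2 study suggesting that Truvada users may have fewer urethral STI symptoms than placebo users. If so, the drug could hold down a symptom-based count while exposure rises.

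**Step 5. Does low baseline condom use hide a fall?** The largest possible fall equals the baseline rate. Complete abandonment of condoms would raise the condomless share by 1/(1 − 0.30) − 1 = 43% from a 30% baseline, 25% from 20% and 11% from 10%. This caps the size of a fall but does not by itself hide one. The power of a two-sided 5% comparison of two proportions, with one yes/no condom indicator per couple, 600 couples at each time and pairing ignored, is:

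| Fall | Power |
|---|---|
| 30% to 25% | 0.49 |
| 30% to 20% | 0.98 |
| 20% to 15% | 0.63 |
| 20% to 10% | 0.998 |

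A 10-point fall would be seen under these assumptions. The finding therefore rests on Steps 1 to 4.

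**The case against.** The best defence is that the protocol names a primary measure, not the sole one. The list of secondary objectives frames 3.2.4 as a move away from condoms, which a condom rate fits. Interviews and monitoring cover other risk behaviour, and the undefined rate can be settled in the statistical analysis plan. Much of this stands: the behaviours are not hidden from the study. What remains is that the protocol itself fixes the measure, and the measure does not match the description it accompanies. Act frequency and outside partners are collected as correlates or covariates, and none is named as an outcome of this objective.

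More acts are also not necessarily risk compensation, since a wish to conceive could explain them. That is a reason for careful reading and does not argue against reporting the change.

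A reader might infer three stronger points that the documents do not support:
- **Condom use here starts below 30%, so at most 180 of 600 couples can show a fall.** The "low condom use (<30%) between partners" in section 1.3 is preliminary information from another project in Jos. No baseline is given for this cohort, two of the three sites are elsewhere, and the unit (couples or acts) is not stated. If it is a share of acts, occasional users can also fall, so 30% × 600 = 180 is no ceiling.
- **More condomless sex or a new partner would read as no change.** STI diagnoses form half of the named measure and might rise. The supportable statement is that such changes could be missed.
- **Risk compensation is measured only by these two items.** Sections 11.5 and 14.3 provide for other risk behaviour to be recorded and watched.

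**Conclusion.** The point holds as a mismatch between definition and measure. The primary measure of Objective 3.2.4 covers less than the risk compensation described under the same objective. On the reading that the condom rate is a share of acts, a rise in condomless acts at a constant rate leaves it at zero, whether that rise is 50% or 100% as in the assumed examples. Outside partners are not recorded by either named item, and the syndromic STI item is too indirect to be relied on for them.

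How often this would happen in the cohort cannot be derived from the protocol, because the act counts are assumed and no baseline is given. The matter concerns a secondary objective and the labelling of outcomes; data collection is largely in place. It is worth correcting because the correction is cheap and prevents a flat condom rate from being read as absence of risk compensation.

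**What to change.** In Objective 3.2.4, keep the condom rate and STI diagnoses, state what the rate is a rate of, and add two named measures:

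1. Change in the number of condomless vaginal acts with the study partner, derived from the sexual frequency and condom use already collected.
2. Change in the proportion of uninfected partners who report any outside partner.

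Take both changes from the enrolment visit, before PrEP starts. Section 11.5 offers PrEP at enrolment, so a month-1 reference would absorb early change. Also show the fall in condom use among couples who used condoms at entry, since the others cannot show one.

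The main cost is wording. The questionnaire should be checked to confirm that condom use is recorded in a form from which condomless acts can be counted. The outside-partner item in Objective 3.2.1 is a yes/no report, which is enough for the second measure. Act counts carry more recall error than a simple condom item, and a rise in condomless acts should be read beside the fertility intentions already collected.

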**Objective 3.2.6: Estimate the resources that would be needed to provide PrEP and TasP for other high-risk groups.**

It is expected that access to the prevention program will be opened to other high risk groups as the program is being rolled out. The cost-effectiveness of providing PrEP and TasP in other high risk groups, such as female sex workers and men who have sex with men, needs to be estimated as decisions are being made about scaling up the project.

*The primary measures of this objective is an estimate of cost per life year gained and cost per infection averted for female sex workers and men who have sex with men.*

## 4.0 Population

A sample with a size of 600 heterosexual HIV-1 serodiscordant couples will be recruited from ART sites with family planning clinics in three States in Nigeria. Couples who had not

---

56. van de Vijver DA, Boucher CA. The risk of HIV drug resistance following implementation of pre-exposure prophylaxis. *Curr Opin Infect Dis.* 2013;23(6):621-627

had prior access to PrEP and couples whom the HIV positive index partner has not been sero-suppressed despite having commenced the use of ARV will be recruited for the study.

## 5.0 Study Sites

The ART sites currently supported by FHI360/SIDHAS and the Harvard/PEPFAR projects will be considered. These sites are the Federal Medical Centre at Nnewi in Anambra State, the Federal Medical Centre in Calabar, Cross Rivers State and the University of Jos, Plateau State. The use of ART sites for study conduct is important so as to ensure ART access by HIV positive partners who are eligible for ART.

One approach to programmatic scale-up of PrEP access within the public sector health service in Nigeria is to integrate its provision into existing service delivery. Integrating HIV prevention into routine outpatient services has several advantages, including:

- Clients would be able to access care and services without undue stigma that is associated with attendance of special clinics like the HIV clinic. Outpatient services are widely available in Nigeria
- The model would enable the project learn about how to provide HIV services as an integrated health care service which can facilitate unbiased attention to both male and females who attend the hospital for health care.

Integrating HIV prevention into HIV care services also has several advantages, including:

- Trained specialized care providers who understand HIV care and service provision would learn to incorporate PrEP and TasP into existing HIV prevention, treatment and care services.
- The HIV index partner can be better managed and monitored over the long term.

Empirical evidence is needed to assess whether integrating PrEP provision into outpatient care services and HIV treatment services can achieve similar levels of safety and PrEP use as observed in the various clinical trials. The study design however, would enable real time changes to be made to implementation plans based on outcomes of the formative assessments as more effective strategies for PrEP access by study populations are identified.

## 6.0 Study Services

Participants will receive baseline and quarterly individual and couples HIV-1 counseling, condoms, risk reduction counseling, and syndromic management of sexually transmitted infections according to local guidelines. HIV-1 infected partners will have quarterly monitoring of HIV-1 clinical status and 6-monthly CD4 counts and will be referred for HIV-1 care based on national HIV-1 care guidelines. Counseling on the importance of not sharing study medications within the partnership will occur at quarterly visits. To reduce interference with the real-world behaviors of the participants, tracing will occur only for follow-up of safety issues and for HIV-1 assessment at the end of the study, but not for

completion of routine visits and PrEP refills. This should allow a more realistic assessment of uptake and adherence.

## 7.0 Eligibility

### 7.1 For heterosexual couples

- Sexually active (defined as having had vaginal intercourse at least 6 times in the previous three months)
- Willing to enter the study as a couple and intending to remain as a couple for the next 12 months
- Has not been on PrEP medication prior to enrollment in study

### 7.2 For HIV-1 uninfected members of the couple (partner participants)

- Able and willing to provide written informed consent
- HIV-1 uninfected based on negative HIV-1 rapid tests, both at study screening and at the enrollment visit
- Adequate renal function, defined by normal creatinine levels and estimated creatinine clearance  $\geq 60$  mL/min
- Not currently pregnant or breastfeeding
- Not currently enrolled in an HIV-1 prevention clinical trial
- Not currently using PrEP
- Enrollment of individuals with active and serious infections or active clinically significant medical problems will be at the discretion of the site investigator

### 7.3 For HIV-1 infected members of the couple (index participants)

- Able and willing to provide written informed consent
- HIV-1 infected based on positive rapid HIV-1 tests, according to national algorithm
- No history of WHO stage III or IV conditions
- Not currently using ART
- Currently using ART but viral load still higher than 5000 copies/ml
- Not currently enrolled in an HIV-1 treatment study.
- Current pregnancy or breastfeeding do not disqualify a candidate who is infected.

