## 2.0 Study Method

This is a demonstration project to evaluate the effectiveness of three models for the delivery of PrEP and TasP as part of a combination prevention strategy for serodiscordant couples in three states in Nigeria. The overall goal is to identify the best model to facilitate uptake of PrEP as part of a comprehensive HIV prevention package for the HIV negative partner in serodiscordant relationships whose HIV positive partner has not begun ART or

---

has been on ART for less than six months. PrEP (daily oral FTC / TDF) will be offered to the HIV-1 uninfected partner. Uptake of PrEP and TasP and adherence to PrEP will be measured. Factors (individual, facility and community level) that facilitate PrEP and TasP uptake and adherence to PrEP will also be assessed.

HIV-1 infected participants will be offered the opportunity to use ART support services regardless of their CD4 count. This is in line with the current national guidelines on HIV treatment for adults and adolescents (2010:13). The current guidelines enable HIV positive individuals in discordant relationships to have access to ART irrespective of the CD4 count. This project will therefore serve as a measure of the effectiveness of this program in Nigeria.

For each couple, if the HIV-1 infected partner initiates ART, we will discontinue PrEP for the HIV-1 uninfected partner six months later (once viral suppression is typically achieved). If the HIV-1 infected partner declines to initiate ART, or initiates and discontinues, we will continue PrEP. Mixed-methods work will be conducted to understand user preferences, couples decision-making, and barriers to uptake of and adherence to both PrEP and ART.

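### PrEP stops on six months of ART alone, so it can be withdrawn while a planned viral load shows viraemia, and the rule for couples admitted viraemic on ART is unclear

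*Protocol*

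**What the plan says.** **The stop.** Section 2.0 says that if the index partner starts ART, "we will discontinue PrEP for the HIV-1 uninfected partner six months later (once viral suppression is typically achieved"). It then gives the only stated grounds for carrying on: "If the HIV-1 infected partner declines to initiate ART, or initiates and discontinues, we will continue PrEP". Section 11.5 words the stop differently: "Once the HIV-1 infected partner has been using ART for 6 months, PrEP will be discontinued for the HIV-1 uninfected partner", after the couple has been counselled. Neither sentence asks for a viral-load result.

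**The measurement.** Viral load is taken from index partners at screening (section 11.4) and in follow-up (section 11.5): "Every 6 months, in addition to regular quarterly visit procedures, CD4 counts and plasma viral loads will be done for HIV-1 infected partners".

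**The strategy.** The Summary ends PrEP once the index partner has achieved suppression, and section 1.5 describes staged use in the same way. The Summary and section 1.4 equate suppression with an undetectable viral load.

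**Entry.** Section 7.3 lists "Not currently using ART" and, as the next item, "Currently using ART but viral load still higher than 5000 copies/ml". Section 4.0 likewise takes couples whose index partner "has not been sero-suppressed despite having commenced the use of ARV". Neither limits time on ART. Section 2.0 describes the target couple as one whose index partner has not begun ART or "has been on ART for less than six months".

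**The concern.** Six months of ART stands in for suppression, and section 1.1 claims suppression within that time only for most people. For the rest, the stop falls due while the index partner can still transmit. The test that would show this is already scheduled but has no bearing on the decision.

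The on-ART entry route makes this sharper. It selects index partners in whom ART has not yet worked, which is the case that the proxy covers least well, and the protocol does not say plainly which stopping rule applies to them.

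Two things are at stake. The first is the protection of an uninfected, sexually active partner. The second is the primary measure of objective 3.1.1, infections averted by PrEP and TasP. Infections after a stop during viraemia, and sites that stop or enrol on different readings, both bear on that measure. Each state runs one delivery model (section 2.0), so a difference in stopping practice between sites could not be told apart from a difference between models.

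**Working it through.** The protocol gives no figure to reproduce here. The check sets the texts side by side and then does simple timing arithmetic.

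**1. Index partners who start ART in the study.** At six months of ART, both 2.0 and 11.5 stop PrEP. Section 2.0 continues it only if ART is declined or given up. An index partner still on ART but viraemic fits neither exception. Section 11.12 stops PrEP only for related serious adverse events, and 11.5 separately stops it at seroconversion, so nothing else covers the case. Section 16.2 lists failing to discontinue product when protocol criteria require it as an example of a violation, so a clinician who continued PrEP would be departing from the protocol.

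**2. Couples admitted on ART.** Two readings are possible.
- *More natural:* the stop concerns ART started in the study. Section 2.0 speaks of initiating ART, and the sentence before the stop in 11.5 is about partners who want to start it. Couples admitted on ART then have no stated stop, and PrEP continues by default.
- *Literal wording of 11.5:* the trigger is six months of ART use, whenever begun. With m months of ART at entry, the stop is due at study month max(0, 6 − m).

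**3. Timing, for illustration.** Assumptions: the stop is acted on at the first visit on or after the due month, and six-monthly viral loads fall on quarterly visits. Section 11.0 (month 1, then quarterly, up to 18 months) allows two calendars:
- A: visits at months 0, 1, 3, 6, 9, 12, 15, 18; viral loads at 6, 12, 18.
- B: visits at months 0, 1, 4, 7, 10, 13, 16; viral loads at 7, 13.

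*ART started in the study at month s; stop due at s + 6.*
- A, s = 1, 2, 3: acted on at month 9. The latest viral load (month 6) was taken at 6 − s = 5, 4, 3 months of ART. The next is at month 12, 3 months after the stop.
- A, s = 7, 8, 9: acted on at month 15. The latest viral load (month 12) was again at 5, 4, 3 months of ART. The next is at month 18, 3 months later.
- A, s = 0, 4, 5, 6: acted on at month 6 or 12, when a viral load is due. If it is unsuppressed, the next is 6 months later.
- B, s = 2, 3, 4: acted on at month 10, latest value at 5, 4, 3 months of ART, next value 3 months later. B, s = 8, 9, 10: acted on at month 16, latest value at 5, 4, 3 months, with no later scheduled value.

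*Couples admitted on ART, literal wording of 11.5:*

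| m at entry | due = max(0, 6 − m) | acted on, A | months to first on-study viral load, A | acted on, B | months to first on-study viral load, B |
|---|---|---|---|---|---|
| 1 | 5 | 6 | 0 | 7 | 0 |
| 2 | 4 | 6 | 0 | 4 | 3 |
| 3 | 3 | 3 | 3 | 4 | 3 |
| 4 | 2 | 3 | 3 | 4 | 3 |
| 5 | 1 | 1 | 5 | 1 | 6 |
| 6 or more | 0 | 0 | 6 | 0 | 7 |

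On this reading the screening value, which was above 5000 copies/ml, is still the latest scheduled viral load at the stop for m of 3 or more on both calendars, and for m = 2 on B.

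**The case against.** **The six-month stop is a disclosed choice.** Section 2.0 gives its reason, section 1.4 uses the same interval and costs PrEP on it, and a fixed time is simple to run in a project meant to resemble routine care. This stands: the stop is not an oversight. It does not answer the case in which a viral load that the study itself collects contradicts the proxy. Section 1.4 argues that PrEP can end without added risk on the basis of an undetectable viral load, not of elapsed time.

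**Loss of suppression is partly handled.** Section 2.0 keeps PrEP going if ART is stopped. This also stands. The gap is limited to index partners who remain on ART and are unsuppressed.

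**A reader might infer that the protocol ends PrEP at enrolment for couples with six or more months of ART.** The documents do not establish that. It takes the sentence in 11.5 apart from the one before it, sets aside the under-six-months description in 2.0, and would defeat the entry route, since 11.5 offers PrEP at enrolment. It is a possible literal reading, not the likely one. The likelier reading has a protective default; its fault is that no end is stated.

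**A reader might also infer that the two ART items in 7.3 contradict each other.** They exclude one another, so they can only be alternatives. The absent conjunction is editorial.

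**Conclusion.** The point holds and should be fixed. It is certain from the text that neither stop has a viral-load condition, that the stated strategy does have one, and that ART duration at entry differs between 2.0 and sections 4.0 and 7.3. For in-study starters the consequence holds on any reading: a scheduled viral load showing viraemia does not keep the partner on PrEP at six months if ART continues. For couples admitted on ART the finding is ambiguity, either no stated end or a stop that could fall during viraemia.

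The size is open. The protocol gives neither the share of couples admitted on ART, nor their time on ART, nor the share unsuppressed at six months, so the number affected cannot be derived. No particular number of infections, or bias in infections averted, should be inferred. The month-by-month timing rests on two constructed calendars and prompt action at visits, and only illustrates the problem.

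**What to change.** 1. Use one ART-duration criterion in 2.0, 4.0 and 7.3: either no limit in all three, or under six months in all three. Adding the conjunction in 7.3 at the same time is a tidy-up.
2. Amend 2.0 and 11.5 so that PrEP stops only when both conditions are met: at least 6 months of ART, whether begun before or during the study, and suppression on the most recent scheduled on-study viral load. Suppression should follow the study's assay definition, not merely a value under the 5000 entry cut-off, and the screening value should not count. Otherwise PrEP continues to the next scheduled viral load.

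**Cost.** One protocol amendment. No tests are added, because 11.5 already schedules the viral loads. The downside is extra donated PrEP where suppression is not shown. For in-study starters this is about 3 months if the last value preceded the stop visit, 6 months if the value at the stop visit is itself unsuppressed, and longer if viraemia persists; late in follow-up, with no further viral load scheduled, it runs to study exit. For couples admitted on ART and suppressed at the first on-study viral load, it is 0 to 6 months (calendar A) or 0 to 7 (B) against the literal reading of 11.5. Against the more natural reading, PrEP becomes shorter once suppression is shown. These figures assume that the result is available at the visit. If it is not, dispensing to the next visit (section 11.3) adds up to about one further quarter.
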